### Statistical analysis

The result will be analysed according to the intention-to-treat (ITT) principle. Per-protocol (PP) analysis will also be conducted as a sensitivity analysis. Baseline characteristics will be described by descriptive analysis and the balance among groups or subgroups will be assessed by analysis for different kinds of data. For continuous variables, the normality distribution will be estimated by using frequency histograms and the Kolmogorov-Smirnov test initially. If the continuous variables are normally distributed, they will be presented as means with standard deviations (SDs). If the continuous variables are non-normally distributed, their medians and interquartile ranges (IQRs) will be reported. For categorical variables, we will present the proportion between each group. In addition, the recruitment number, those participants lost to follow-up, protocol violations and other relevant data will also be reported. A comparison between groups will be performed using the independent sample *t*-test, Mann-Whitney *U* test for continuous variables or Pearson chi-square test/Fisher’s exact test for categorical variables as appropriate. The primary outcome will be compared using Pearson’s chi-square test or Fisher’s exact test as appropriate. Categorical secondary outcomes will be compared between two groups using a similar approach as the primary outcome. Student’s *t*-test or Wilcoxon test will be used as appropriate for continuous secondary outcomes, such as birth weight, etc. The relative risks (RR) and absolute rate differences (ARD) and their 95% confidence interval (CI) between the two groups will be calculated. And the 99% CI of the ARDs will be used to evaluate if the letrozole group is superior to the control group. Multiple variable logistic regression models will be used to assess the treatment effect adjusting for other potential confounding variables that are unbalanced in the baseline.

Missing data will be treated as missing at random and will be imputed using the last observation carried forward (LOCF) method. For the missing values, a sensitivity analysis will be done under the hypothesis of the worst and the best outcomes for each missing individual. Therefore, all secondary outcomes will be considered exploratory. All statistical analyses will be done using the statistical package SPSS (version 26.0, released 2019, IBM corp., Armonk, NY, USA). Statistical significance is defined as *p* < 0.05 with two-sided testing.

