### Embryo transfer and luteal support

Fresh embryo transfer or elective freezing of all embryos will be decided by physicians according to the conditions of women. All embryos will be cryopreserved without fresh transfer when the women are at risk of OHSS, have elevated serum progesterone level on the trigger day (> 1.5 ng/L or > 5 nmol/L) or had endometrial polyps or fluid in the uterine cavity. To reduce the risk of multiple pregnancies, up to two embryos will be transferred on day 2/3 and one blastocyst will be replaced on day 5. Excess cleavage stage embryos will be vitrified or further cultured to the blastocyst stage while excess blastocyst will be vitrified accordingly.

In women with fresh embryo transfer, the luteal phase is supported with vaginal progesterone gel (Crinone, Merck Serono) at a dose of 90 mg daily or oral progesterone (Duphaston, Abbott) at a dose of 10 mg three times daily from the day of oocyte retrieval until the day of serum or urine hCG test.

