### Follow-up

Transvaginal ultrasonography will be performed 2 weeks after a positive serum or urine pregnancy test to confirm intrauterine pregnancy. Scanning will be repeated later to confirm ongoing pregnancy, which is defined as a viable pregnancy with a foetal heartbeat at 10–12 weeks. Information regarding the outcome of the pregnancy and obstetrical and perinatal complications will be obtained through a review of obstetrical medical records and neonatal medical records. The live birth is defined by the live foetus in the uterine after 20 weeks of gestation.

We will collect the following information within 6 weeks after delivery, including antenatal information (pregnancy complications and foetal information), delivery information (gestational age, mode of delivery, placental weight and birth complications) and newborn information (foetal sex, birth weight and birth defects).

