OHSS	It is classified as mild, moderate or severe according to the degree of abdominal distention, ovarian enlargement and respiratory haemodynamic, and metabolic complications. Diagnosed by ultrasound, blood testing and physical examination according to the RCOG Guideline
Ectopic pregnancy	A pregnancy outside the uterine cavity, diagnosed by ultrasound, surgical visualisation or histopathology
Obstetric and perinatal complications	
Hypertensive disorders of pregnancy	Including pregnancy-induced hypertension, preeclampsia and eclampsia
Antepartum haemorrhage	Including placenta previa, placenta accreta and unexplained
Multiple pregnancies	Pregnancy with more than one foetus
Birth weight	Including low birth weight (weight < 2500 g at birth), very low birth weight (< 1500 g at birth), high birth weight (> 4000 g at birth) and very high birth weight (> 4500 g at birth)
Small for gestational age	Birth weight less than the 10th centile for the sex-specific birth weight for a given gestational age reference
Preterm delivery	Birth of a foetus delivered after 28 and before 37 completed weeks of gestational age
Congenital anomaly	Structural or functional disorders that occur during intrauterine life and can be identified prenatally, at birth or later in life, including trisomy 21 syndrome, neural tube defect, congenital heart disease, cleft lip, excessive numbers of fingers or toes and hydrocephalus
Perinatal mortality	Foetal or neonatal death occurring during late pregnancy (at 28 completed weeks of gestational age and later), during childbirth, or up to seven completed days after birth

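### Plain two-sample tests for birth weight and other newborn outcomes make no provision for twins: precision is overstated if babies are analysed separately, and growth is mixed with twin rate in any case

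*Protocol article*

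**What the plan says.** All references are to the Protocol article.

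- **Tests.** The Statistical analysis section names Student's t-test or a rank test for continuous secondary outcomes and uses birth weight as its example: "Wilcoxon test will be used as appropriate for continuous secondary outcomes, such as birth weight, etc". For the rest, "Categorical secondary outcomes will be compared between two groups using a similar approach as the primary outcome", which means Pearson chi-square or Fisher's exact test.
- **Source of twins.** Under Embryo transfer and luteal support, "up to two embryos will be transferred on day 2/3 and one blastocyst will be replaced on day 5". Table 2 lists multiple pregnancies as a secondary outcome ("Pregnancy with more than one foetus").
- **Newborn outcomes.** Follow-up collects "newborn information (foetal sex, birth weight and birth defects". Table 2 defines SGA as "Birth weight less than the 10th centile for the sex-specific birth weight for a given gestational age reference" and preterm delivery as "Birth of a foetus delivered after 28 and before 37 completed weeks of gestational age". It also lists low birth weight, congenital anomaly and perinatal mortality. None is restricted to singletons.
- **Adjustment.** The only regression planned is logistic, "adjusting for other potential confounding variables that are unbalanced in the baseline". Plurality arises after randomisation and so falls outside it.
- **Status.** The Statistical analysis section classes every secondary outcome as exploratory, but still plans 95% confidence intervals and a two-sided 5% significance level.

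The article does not say whether the unit for these outcomes is the baby or the woman, and it does not mention correlation between twins or separation by plurality.

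**The concern.** The named tests assume independent observations. Twins share a mother and a gestational age, so two weights from one pregnancy carry less information than two weights from different pregnancies. Entered as separate rows, they make the standard error too small.

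The second problem does not depend on the unit. Twins are generally lighter than singletons, so a difference in twin rate between arms shifts mean birth weight and the SGA proportion even if letrozole has no effect on growth. The Background links high estradiol to SGA in singleton pregnancies. The planned comparison pools singletons and twins, so it does not isolate the association that motivates the outcome.

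At stake is a neonatal signal, favourable or unfavourable, that reflects overstated precision or a different twin rate and not fetal growth.

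**Working it through.** **The plan's own figure.** The article gives no figure for newborn outcomes. Its primary sample size reproduces and supplies the number of deliveries. For 35% v 45%, one-sided 2.5% and 80% power, with pooled variance:

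n = [1.96·√(2·0.40·0.60) + 0.8416·√(0.35·0.65 + 0.45·0.55)]² / 0.10² = (1.358 + 0.580)² / 0.01 ≈ 376 per arm, as stated.

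At 450 per arm this implies 450 × 0.35 ≈ 158 and 450 × 0.45 ≈ 203 women with a live birth. If 20% have no fresh transfer, the figures are 360 × 0.35 = 126 and 360 × 0.45 = 162.

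**Assumed inputs (none in the document).** Twin share of deliveries t = 5-30%; within-pair correlation r = 0.3-0.8; birth weight SD 500 g; twin deficit 750-800 g.

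**Step 1: correlation alone, each baby a separate row.**

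Design effect DE = [(1−t) + 2t(1+r)] / (1+t) = 1 + 2tr/(1+t). True error of a nominal 5% test = 2·[1 − Φ(1.96/√DE)].

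| t | r | DE | True SE / naive SE | True error |
|---|---|---|---|---|
| 5% | 0.3 | 1.03 | 1.01 | 5.3% |
| 10% | 0.5 | 1.09 | 1.04 | 6.1% |
| 20% | 0.5 | 1.17 | 1.08 | 7.0% |
| 30% | 0.7 | 1.32 | 1.15 | 8.8% |
| 30% | 0.8 | 1.37 | 1.17 | 9.4% |

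**Step 2: shared lower weight of twins left in, equal twin rates.** Both twins carry the same deficit, which adds to their similarity in a pooled analysis. Simulation with an 800 g deficit, 158 deliveries per arm, t = 5-30%, r = 0.3-0.7 and 4,000 replicates:

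- t-test on babies: true error 7.2-10.0%; true SE 1.09-1.20 times the naive SE.
- One mean per woman, or singletons only: 4.5-5.8%, close to nominal.

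**Step 3: unequal twin rates, no effect on growth.** The twin share of babies is 2t/(1+t). For 20% v 25% twin deliveries it is 0.333 v 0.400, and 0.067 × 750 g ≈ 50 g. A simulation with 20% v 30%, an 800 g deficit, r = 0.5 and 158 v 202 deliveries gave a mean difference of about −104 g. It was declared significant in 43% of runs per baby, 26% per woman and 5% in singletons only.

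**Step 4: could the twin rates differ?** As an illustration only, suppose every woman receives two embryos and each leads to a birth independently with probability p. Then 1 − (1−p)² = 0.35 gives p = 0.194, and 0.45 gives p = 0.258. In this model p is also the twin share of babies, so a 750 g deficit implies a shift of (0.258 − 0.194) × 750 ≈ 48 g against letrozole from the hypothesised gain in live births alone. The shift shrinks as more women receive a single blastocyst.

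**The case against.** A reader might infer that the standard errors are definitely too small for every newborn outcome. The document does not support that. It does not fix the unit of analysis. Anomaly, perinatal death, low birth weight and SGA can each be counted once per woman, and birth weight can be reduced to one value per woman. Categorical outcomes are to follow the approach of the primary outcome, which is a proportion of women. On that reading chi-square and Fisher are valid and the standard-error problem disappears, as Step 2 confirms. This part of the objection stands, so the error-rate figures are conditional.

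A reader might also infer that the pooled comparison is invalid. It is not. Plurality arises after randomisation, so a pooled contrast is a legitimate total effect among births, and the 43% and 26% in Step 3 are not false positives for that quantity. They are misleading only if read as effects on growth. A singleton-only comparison itself conditions on a post-randomisation event. The multiple-pregnancy rate by arm is already a planned outcome.

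Two further points stand. All magnitudes rest on assumed inputs, concern birth weight and are small at low twin rates. The outcomes are exploratory and numerous, so a modest inflation on a few of them does not alter the trial's main conclusion.

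It could be said that the unit and the handling of twins belong in an analysis plan that is not shown. That carries less weight here. The article names the tests for birth weight itself, collects weight and defects for the newborn, and words preterm delivery per foetus. The separate day 3 and day 5 results promised in the Discussion do not help, because day 3 transfers still mix singletons and twins.

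**Conclusion.** The point holds in a conditional form. The tests named for newborn outcomes do not fit data that will include twins if each baby is a separate observation. For twin shares of 5-30% and within-pair correlations of 0.3-0.8, both assumed, a nominal 5% test then runs at roughly 5-9%. With an assumed 800 g twin deficit left in, the simulated figure is 7-10%. Whatever the unit, the pooled comparison cannot separate an effect on growth from a difference in twin rate; about 50 g would follow from an assumed 20% v 25% twin rate and a 750 g deficit. That matters because the stated rationale concerns singletons.

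The consequence is confined to exploratory neonatal outcomes. The primary outcome, counted per woman, is unaffected, and nothing here supports a claim that the trial's main conclusion is at risk. Exploratory status does not make a wrong interval right, so the change is worth making but is not critical.

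**What to change.** - **Birth weight, low birth weight and SGA:** state the unit of analysis and replace the plain tests with a GEE or mixed model that clusters babies within mother, with a robust standard error.
- **Plurality:** clustering corrects the standard error but not the mixing. Add a singleton-only comparison, read it beside the already planned multiple-pregnancy rate by arm, and note that plurality is a post-randomisation event.
- **Sparse outcomes (congenital anomaly, perinatal death):** count once per woman (any affected baby) and keep Fisher's exact test. Clustered models can be unstable with few events.

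The cost is a few sentences in the analysis section, no new data, slightly wider intervals and a little more analysis work.

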### Randomisation and allocation concealment

Recruited women will be randomly allocated in a 1:1 ratio to the letrozole group or the control group according to a computer-generated randomisation list put in opaque sealed envelopes which are open consecutively for eligible participants after screening. Both investigators and participants are aware of the allocation of the intervention. The biostatistician performing the data analysis will be blinded to the group allocation.

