### Statistical analysis

#### Sample size calculation

The primary hypothesis of this trial is that the letrozole group will increase the live birth rate when compared with the control group. This treatment will be considered effective if the proportion of women having a live birth is increased by 10% in absolute terms. With an 80% power and a one-sided 2.5% level of statistical significance, we will need to recruit 752 women (376 in each arm) to show an absolute difference of 10% from 35 to 45% between control and letrozole groups. Taking consideration of the dropout rate as 20% (such as cancellation of fresh embryo transfer because of high risk of OHSS), each group will include 450 women (a total of 900 women).

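### Superiority is to be judged on a 99% confidence interval, but the trial is sized at one-sided 2.5% and tests at two-sided 5%; the primary verdict is ambiguous, and under the 99% rule power is about 57–69%, not 80%

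*Protocol article*

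**What the plan says.** The protocol article sets a level of evidence for the primary comparison in three places.

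- **Sample size calculation:** "With an 80% power and a one-sided 2.5% level of statistical significance, we will need to recruit 752 women (376 in each arm"). The effect assumed there is a rise in live birth from 35% (control) to 45% (letrozole). After a 20% allowance for dropout, "each group will include 450 women (a total of 900 women").
- **Statistical analysis, first paragraph:** "The primary outcome will be compared using Pearson’s chi-square test or Fisher’s exact test as appropriate". Relative risks and absolute rate differences (ARD) are to be given with 95% confidence intervals. Then: "And the 99% CI of the ARDs will be used to evaluate if the letrozole group is superior to the control group".
- **Statistical analysis, last paragraph:** significance is defined as p "< 0.05 with two-sided testing".

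The main analysis is by intention to treat, and secondary outcomes are exploratory.

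**The concern.** One-sided 2.5%, two-sided 5% and a two-sided 95% interval are the same criterion for superiority. Requiring a two-sided 99% interval to exclude zero is a one-sided 0.5% test, five times stricter than the level used for sizing. It is also the only sentence in the analysis section that says how superiority will be decided, so it cannot be passed over as a reporting detail.

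The article describes no interim analysis, alpha spending or co-primary outcome that would account for the stricter level.

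Two things are at stake. If the 99% sentence is followed, the trial falls well short of its stated power. If nobody settles which sentence governs until the data are in, the threshold for the primary claim is open to choice, in an open-label trial whose investigators know the allocation.

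**Working it through.** **Inputs** (Sample size calculation; 1:1 ratio from Randomisation and allocation concealment): control rate 0.35, letrozole rate 0.45, difference d = 0.10, power 80%, 376 per arm before dropout, 450 per arm recruited, dropout 20%. Hence 450 × 0.80 = 360 per arm if the dropout occurs as planned.

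**1. Reproduce the stated sample size.** With pooled variance under the null and no continuity correction:

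n = [z_α √(2 × 0.40 × 0.60) + z_β √(0.35 × 0.65 + 0.45 × 0.55)]² / d²

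= [1.960 × 0.6928 + 0.8416 × 0.6892]² / 0.01 = 375.6, so 376 per arm and 752 in total.

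This matches the article exactly. The design level is therefore one-sided 2.5% (equivalently two-sided 5%).

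**2. Sample size that a 99% interval would need.** Replace 1.960 by 2.576:

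- Pooled: [2.576 × 0.6928 + 0.8416 × 0.6892]² / 0.01 = 559.2, so 560 per arm.
- Unpooled: (2.576 + 0.8416)² × 0.475 / 0.01 = 554.8, so 555 per arm.

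Allowing for 20% dropout, 560 / 0.80 = 700 per arm, or 1,400 women, against the planned 900.

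**3. Power at the planned sizes.** Using the interval for the difference, SE = √(0.475 / n) and power = Φ(0.10 / SE − z):

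| Women per arm | SE | Power, 95% CI rule | Power, 99% CI rule |
|---|---|---|---|
| 360 (450 less 20%) | 0.0363 | 78.6% | 57.0% |
| 376 | 0.0355 | 80.3% | 59.4% |
| 450 | 0.0325 | 86.8% | 69.2% |

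The pooled formula gives 78.3%, 80.0% and 86.6% under the 95% rule, and 56.5%, 58.9% and 68.7% under the 99% rule.

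Reading the 99% figure as a one-sided bound (z = 2.326) gives about 69% at 376 and 77% at 450. No reading of 99% reaches 80% with the planned numbers.

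**4. Where the two rules disagree.** With 450 per arm at the design rates, the observed difference must exceed 1.960 × 0.0325 = 6.4 points for the 95% interval to exclude zero, and 2.576 × 0.0325 = 8.4 points for the 99% interval. With 376 per arm the limits are 7.0 and 9.2 points.

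An example with 450 per arm: 162 live births (36.0%) against 195 (43.3%), a difference of 7.3 points.

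- Pooled SE = √(2 × 0.3967 × 0.6033 / 450) = 0.0326, z = 2.25, two-sided p = 0.025.
- Unpooled SE = 0.0325. The lower limit is +1.0 point for the 95% interval (7.3 − 6.4, from unrounded values) and −1.0 point for the 99% interval (7.3 − 8.4).

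The result is significant by the last paragraph of the section and not superior by the first.

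**5. How often this would happen.** In 1,000,000 simulated trials at 35% versus 45%, p was below 0.05 in favour of letrozole while the 99% interval still included zero in 17.4% of trials with 450 per arm, 20.4% with 376 and 21.3% with 360.

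**The case against.** The strongest points on the other side are these.

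- **The power loss is conditional.** It arises only if the 99% sentence governs. Under the two-sided 5% rule, power is 80.0% at 376 and 86.6% at 450 per arm (pooled). This stands: what is established outright is an ambiguous decision rule, and the loss of power is one branch of it.
- **A 99% interval is conservative.** This also stands. Type I error is not inflated; the risk is a missed effect or a disputed verdict.
- **The 99% level may have been deliberate.** The article is a condensed text. Its remark that secondary outcomes are exploratory follows on from nothing before it, so a multiplicity rationale may have been lost, and the 99% sentence speaks of ARDs in the plural. That is possible, but a rationale would not remove the conflict with the sample size, which was plainly not computed at that level.
- **The 95% rule does not guarantee 80% power either.** The sample size section counts cancelled fresh transfers as dropout ("Taking consideration of the dropout rate as 20% (such as cancellation of fresh embryo transfer because of high risk of OHSS")), while the analysis is by intention to treat. If, as an assumption, that 20% of women count as having no live birth, the rates become 0.8 × 35% = 28% and 0.8 × 45% = 36%. Power at 450 per arm is then about 73% under the 95% rule and 50% under the 99% rule. This is a fair caution: aligning the level removes the contradiction but does not secure the power.
- **Relaxing a published threshold late is itself delicate.** The article reports 890 women already recruited, and allocation is known to investigators. This affects how the change must be made, not whether it is needed.

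**Conclusion.** The concern holds. The article gives two incompatible criteria for its primary conclusion. The sample size level and the significance level agree with each other, and the 99% interval is the outlier.

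If the 99% rule is followed, power is about 57% (360 per arm), 59% (376) or 69% (450), against a stated 80%. If the design effect is true, there is a 17–20% chance, for 450 down to 376 per arm, that the two rules give different answers.

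These figures assume the design rates of 35% and 45%, equal arms and normal-approximation intervals. Under the dilution assumption described above, power with the 99% rule falls to about 50%. Because the point decides the primary claim, it should be settled before database lock.

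**What to change.** Remove the 99% sentence and state one rule. For example: superiority will be declared if the lower limit of the two-sided 95% confidence interval for the absolute difference in live birth rate (letrozole minus control), in the intention-to-treat population, is above zero. This matches the one-sided 2.5% used for sizing and the two-sided 5% significance level. Add that the 10-point difference in the sample size section is the design effect and not a further threshold, since with 450 per arm the 95% rule can be met at about 6.4 points.

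If the sponsor prefers to keep 99%, it should give the reason, drop two-sided 5% as the criterion for the primary outcome, and restate power as about 57–69% for the planned numbers. With 890 of 900 women recruited at the time of writing, enlarging the trial to about 1,400 is hardly practical.

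Either way, record the choice in a dated amendment, with a statement that it was made before anyone had seen outcomes by arm. The article expected data collection to run to February 2023, so on its own timeline the change could be made before database lock. The cost is one sentence in the analysis section and the amendment itself, with no further patients or data.

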**Methods/design:**

This is an open-label randomised controlled superiority trial being performed in two assisted reproduction centres in China. Infertile women who have antral follicle count (AFC) before ovarian stimulation or on day 5 of ovarian stimulation ≥15 are randomly allocated in a 1:1 ratio to receive either letrozole and FSH or FSH alone in a GnRH antagonist protocol. Recruited women follow the standard operating procedures of the two centres. The primary outcome is the live birth rate of the fresh embryo transfer. Stimulation parameters, maternal side effects and obstetric and perinatal complications are secondary outcomes. The planned sample size is 900, i.e. 450 per group.

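### The supportive logistic model takes its covariates from observed baseline imbalance, so chance decides its content and factors such as centre and age will usually be left out; the unadjusted primary test is unaffected

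*Protocol article*

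**What the plan says.** All of this is in the protocol article.

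- Statistical analysis, primary comparison: "The primary outcome will be compared using Pearson’s chi-square test or Fisher’s exact test as appropriate". No covariate and no centre term is attached to it.
- Same section, further model: "Multiple variable logistic regression models will be used to assess the treatment effect", with covariates entering by "adjusting for other potential confounding variables that are unbalanced in the baseline".
- Same section, how imbalance is judged: "the balance among groups or subgroups will be assessed by analysis for different kinds of data". No threshold or criterion is given, and no variable is named for adjustment here or elsewhere.
- Abstract, Methods/design: "This is an open-label randomised controlled superiority trial being performed in two assisted reproduction centres in China".
- Randomisation and allocation concealment: women are "randomly allocated in a 1:1 ratio to the letrozole group or the control group according to a computer-generated randomisation list". No stratification is stated. Investigators and participants know the allocation; the biostatistician who analyses the data does not.
- Inclusion criteria: age under 42, and an AFC of at least 15 taken either before stimulation or on stimulation day 5.

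**The concern.** Proper randomisation leaves chance as the only source of baseline differences between the arms. A rule that adjusts for whatever differs therefore responds to noise. It takes no account of how strongly a variable predicts live birth, which is what determines whether adjustment helps. A strong predictor that happens to be balanced is left out; a weak one that happens to be unbalanced goes in.

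Two things are at stake. First, the adjusted estimate has no form fixed in advance. Its covariates, and with a logistic model the meaning of its odds ratio, depend on the realised allocation and on an unstated criterion for imbalance. Second, the precision that a fixed model would bring is mostly forgone. Centre is the clearest case: there are two centres, no stated stratification, and no centre term in any analysis unless centre happens to be unbalanced.

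This is a selection rule that the protocol states, not a detail left to an analysis plan. A plan that followed it would inherit the problem.

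**Working it through.** **1. The plan's own figure.** The sample size is not in dispute; reproducing it sets the scale. Inputs from Sample size calculation: "absolute difference of 10% from 35 to 45% between control and letrozole groups", 80% power, one-sided 2.5%. With mean rate 0.40:

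n per arm = [1.960·√(2·0.40·0.60) + 0.842·√(0.35·0.65 + 0.45·0.55)]² / 0.10² = 375.6, rounded up to 376. This matches the protocol.

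**2. How often the rule changes the model.** Assumptions not in the document: k independent baseline variables, each flagged at p < 0.05. P(at least one flagged) = 1 − 0.95^k.

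| k | P(at least one flagged) |
|---|---|
| 3 | 14.3% |
| 5 | 22.6% |
| 10 | 40.1% |
| 15 | 53.7% |

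Under the same assumptions any one variable enters with probability 5%, so a given prognostic variable is omitted about 95% of the time. In the simulation below the leading prognostic variable was selected in 4.5% to 5.3% of runs.

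**3. What the rule costs.** Simulation with 900 women, 4,000 runs per scenario, and ten independent baseline variables of which two are prognostic. The first has log odds ratio b per SD and the second b/2. The conditional treatment log odds ratio is 0.42, close to the design value: ln(0.45/0.55) − ln(0.35/0.65) = 0.418. The values of b are assumptions.

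| b | Power, unadjusted | Power, imbalance-selected | Power, two fixed covariates |
|---|---|---|---|
| 0.3 | 85.1% | 85.3% | 86.1% |
| 0.6 | 79.8% | 79.8% | 83.2% |
| 0.9 | 72.2% | 73.0% | 80.2% |

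Compare across a row only: with the conditional effect held at 0.42, the unadjusted log odds ratio shrinks as b grows (mean 0.410, 0.383, 0.348), which by itself lowers unadjusted power. Within each row, the imbalance rule performs almost like no adjustment. In the last row its mean log odds ratio is 0.353, against 0.423 with fixed covariates.

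**4. Type I error.** With no treatment effect, rejection rates in the three scenarios were 4.9%, 4.9% and 5.4% unadjusted; 4.8%, 4.9% and 5.0% imbalance-selected; and 5.0%, 5.1% and 5.2% with fixed covariates. The Monte Carlo standard error is √(0.05·0.95/4000) = 0.34 points, so none departs from 5%.

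**5. Precision expressed in women.** If the fixed covariates explain a share R² of outcome variance, the approximate gain is 900·R²/(1 − R²).

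- R² = 2.6%: 900·0.026/0.974 = 24 women
- R² = 5%: 900·0.05/0.95 = 47 women
- R² = 10%: 900·0.10/0.90 = 100 women

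To link this to step 3, take R² = Var{expit(a + sZ)}/(0.40·0.60), with Z standard normal, s² = b² + (b/2)², and a set so that the mean rate is 40%. Numerical averaging gives R² of about 2.6%, 9% and 17% for b = 0.3, 0.6 and 0.9. The first two rows of the power table therefore span roughly the 2.5% to 10% range, where a fixed model gains about 1 to 3 points over the imbalance rule. The third row is stronger than that range.

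**The case against.** The strongest reply is that nothing decisive depends on this model. The primary comparison is an unadjusted chi-square or Fisher test, and neither the p-value criterion nor the 99% interval for the rate difference is described as covariate-adjusted. That stands, and it limits the point to a supportive analysis.

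Further replies that stand in whole or part:

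- A reader might infer that the rule makes the trial's conclusion invalid or inflates false positives. The document gives the primary conclusion to an unadjusted test, and step 4 shows rejection rates near 5% under all three approaches.
- A reader might infer that, because the trial is open-label, the analyst can freely choose the more favourable model. The biostatistician is stated to be blinded to allocation. This reduces the room for choice but does not specify the model, and choices made after unblinding remain possible.
- A reader might infer that any irrelevant variable can enter. The rule is limited to potential confounders, so there is a filter as well as imbalance. But the potential confounders are not listed, so the filter does not fix the model.
- A reader might infer that baseline significance tests are prescribed. The wording on balance does not say so; the 5% threshold used above is an assumption.
- An unadjusted primary test that omits centre is valid. A condensed article may also leave out a stratification that exists, so no ignored design factor can be claimed.
- The document does not itself call centre or age prognostic. That is general trial knowledge, and the fault in the rule does not depend on which variables are named.
- AFC is not a ready-made covariate, because the inclusion criteria allow two measurement times.

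**Conclusion.** The point holds for the supportive adjusted analysis. The stated rule lets chance choose the model, usually omits prognostic variables, and gains almost nothing over no adjustment. The harm is lost precision and an adjusted estimate with no form fixed in advance. It does not reach the validity of the primary test.

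The size depends on assumptions that the document does not supply. The flagging probabilities of 14% to 54% assume 3 to 15 independent variables and a 5% threshold; they show how often the model would change, not a bias. The gain of roughly 24 to 100 women out of 900 assumes R² of about 2.5% to 10%. Eligibility already restricts age and AFC, so the lower end should be kept in view. It is worth correcting because the correction is nearly free.

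**What to change.** Replace the imbalance rule with one fixed model: logistic regression of live birth on arm, centre and female age, in all women randomised, reported as a standardised risk difference and relative risk with 95% CIs. AFC may be added if the plan names a single measurement time before letrozole starts; otherwise leave it out. State that baseline significance tests will not be used to choose covariates. State that the unadjusted test carries the primary conclusion and that the adjusted model is supportive. Fix all this before outcome data are unblinded; the article reports 890 women already recruited and data collection running to February 2023.

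The cost is wording, plus possibly a little programming for the standardised estimates. Centre is known and age is needed for eligibility, so no new data are required, and the sample size does not change. The one item that needs a check is whether AFC at a single time point is available for every woman.
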